##### Muscle biopsy

2.6.3.2

Skeletal muscle biopsies of the vastus lateralis are optional, where participants are asked at the time of consent if they wish to partake. Skeletal muscle-derived biomarkers to be assessed include myokines [IL-6, IL-15, secreted protein acidic and rich in cysteine (SPARC), oncostatin M (OSM), decorin, irisin] and insulin pathway-related biomarkers (GLUT-4 receptors, IGF-1, IGFBP-3). The muscle biopsy is performed by a qualified nurse practitioner and/or physician assistant.

The local area (quadriceps thigh muscle) is anesthetized with a numbing spray, followed by an injection of lidocaine. A cannula (∼13.5-gauge) is then inserted into the vastus lateralis muscle perpendicularly, such that it pierces through the layer of fascia surrounding the muscle fibers. To obtain the biopsy, the needle is fed through the cannula, and the biopsy trigger is activated, resulting in a spring-loaded, rapid collection of ∼10–15 mg muscle tissue. The cannula remains inserted into the muscle, the needle is removed, and the procedure is repeated until an adequate sample is collected. After sampling is complete, the cannula is removed, and pressure is applied to the area to stop any potential bleeding, with a bandage placed over the biopsy site to promote healthy healing. The muscle sample is briefly washed on clean gauze and frozen using liquid nitrogen for storage at −80°C for later batched analysis. The biopsies occur following a 12 h fast. The post-intervention biopsy is performed at a distance of ∼1 cm from the first incision and 72–96 h after the last training session for participants in the exercise to reflect resting levels of mRNA expression (43).

#### Exploratory outcomes

2.6.4

##### Prostate cancer cell proliferation

2.6.4.1

The proliferation rate of LNCaP cells is assessed using plasma samples at baseline and at post-intervention. LNCaP cell line is grown in ATCC-formulated RPMI 1640 media supplemented with 5% fetal calf serum (FCS) and 1% penicillin–streptomycin (ATCC Manassas, VA, USA). LNCaP cells (100 µL) are seeded at a concentration of 50,000 mL in a 96-well plate containing either 5% FCS with or without the addition of 5% human plasma from test subjects in triplicate for 48 h to determine cell proliferation. As an alternative, patient serum collected could be used in lieu of FCS, and this will be experimentally determined. After plating the same number of cells for a defined period of time, final cell numbers will be determined by removing supernatant and fixing cells with 100 µL 4% paraformaldehyde in the plate for 20 min. Fixed cells are then incubated for an additional 20 min with 100 µL 2% crystal violet (Thermo Fisher Scientific, Edmonton, Canada) dye solution (0.1%, w/v, with ethanol 2%, v/v in 0.5 M Tris-C1, pH 7.80) (44). The stained cells are washed in tap water and solubilized with an SDS solution (0.1%, w/v, with ethanol 50%, v/v, in 0.5 M Tris-C1, pH 7.8; 100 µL per well) for 30 min. The crystal violet dye is released by the fixed cells into the supernatant, and the absorbance is measured by a Molecular Devices spectrophotometer (San Jose, CA, USA) at 600 nm.

#### Covariates

2.6.5

##### Participant characteristics, health behaviors, and medical history

2.6.5.1

Participant demographic and medical history data were collected at baseline from medical records, and participants completed questionnaires. Information collected includes age, gender, race, ethnicity, non-cancer medical history, cancer history, family cancer history, anthropometric history, smoking habits, alcohol intake, medication use, and vitamin and supplement use.

##### Anthropometrics

2.6.5.2

Body composition is assessed via bioelectrical impedance analysis (BIA) using a validated device (Tanita 780, Arlington Heights, IL, USA). The device estimates body fat using an algorithm based on the user’s age, sex, height, and body weight. Waist and hip circumference is also obtained using a constant-tension tape measure.

##### Participant-reported outcomes

2.6.5.3

Health-related quality of life is assessed using the European Organization for Research and Treatment of Cancer Quality of Life Questionnaire-C30 (45). A higher functional score represents a healthier level of functioning, a higher global health status represents a higher quality of life, and a higher symptom scale represents a higher level of symptoms. Sleep quality is assessed using the Pittsburgh Sleep Quality Index (PSQI), which contains 19 questions evaluating seven domains of sleep—subjective sleep quality, sleep latency, sleep duration, habitual sleep efficiency, sleep disturbances, use of sleep medication, and daytime dysfunction (46, 47). The Functional Assessment of Cancer Therapy—Bone Pain (FACT-BP) is used to assess cancer-related bone pain and its effect on quality of life (48). The Brief Pain Inventory (BPI) is used to assess the impact of general pain on quality of life. The BPI includes a sensory and reactive dimension and has been previously validated in breast cancer survivors (49). The Exercise Benefits/Barriers Scale (EBBS) is used to assess barriers to exercise (50). Finally, the expanded Prostate Cancer Index Composite-26 is used to measure health-related quality of life across five prostate cancer-specific domains (51).

##### Cardiorespiratory fitness

2.6.5.4

To assess maximal oxygen consumption (VO_2peak_) and accurately prescribe the intensity for the self-directed aerobic exercise, a maximal cardiopulmonary exercise test is completed on a cycle ergometer (ErgoSelect 100; Ergoline) using an incremental ramp protocol (52). Participants complete a 3 min warm-up with no resistance and then start the ramp protocol at 10 W and proceed into an incremental ramp protocol increasing 10 W every minute until volitional fatigue. Cadence is kept between 60 and 70 revolutions per minute. Heart rate (HR; FT4; Polar, USA) and rate of perceived exertion (Borg scale 1–10) are recorded every minute and at the end of the test. Expired gas analysis (TrueOne 2400; ParvoMedics, Inc.) is used to measure VO_2peak_. The results of this test are used to calculate the target heart rate for the self-directed aerobic exercise.

##### Physical function

2.6.5.5

Functional power is measured using a stair climb test that has been successfully performed and correlated with lower-extremity power and mobility performance in older adults (53). Participants are instructed to ascend a flight of 10 stairs one step at a time as quickly as possible. Timing begins when one foot steps on the third stair and ends when one foot reaches the ninth stair. Time is recorded to the nearest 0.01 s, where three trials are completed, and the fastest is used to calculate power (54).

Mobility is assessed using the Timed Up and Go (TUG) test, which has been shown to predict immediate fall risk better than static balance tests or isometric muscle strength (55). Participants begin seated in a chair, walk to a line on the floor 3 m from the chair, turn around, and return to the same seated position as quickly and safely as possible. Scores are taken as the time to complete the task once, where an average of the time for three trials is calculated.

##### Muscular strength

2.6.5.6

Grip strength is measured using a handheld dynamometer on the participant's dominant hand. The subject is asked to grip the handle of the dynamometer with one hand using as much grip pressure as possible while holding for 3–5 s. The average of three attempts is calculated.

One repetition maximum (1 RM) is estimated from 10 RM muscle strength tests on two exercises: (1) leg press and (2) chest press. One RM values are calculated and reported using validated equations (56, 57). Following a warm-up, a maximum of five attempts is given to reach the final 10 RM load with a 1–2 min rest period between attempts.

##### Physical activity

2.6.5.7

Participants are provided an accelerometer (ActiGraph, Pensacola, FL, USA) to wear for 7 days at all times except for when swimming, bathing, and/or sleeping. The device records activity data and is electronically transferred to a computer via USB cable at the time of completion. In addition, control participants are also given weekly physical activity logs to complete over the initial 16-week intervention period.

##### Diet

2.6.5.8

An automated self-administered 24 h dietary assessment tool is used to assess recent dietary patterns for two weekdays and one weekend day (58). This is completed via an online portal over 3 non-consecutive days where possible.

##### Exit survey

2.6.5.9

A study-tailored questionnaire evaluating intervention satisfaction is provided at post-intervention testing only. This survey includes questions related to the following: (1) timing of the intervention; (2) length of sessions; (3) telephone-based approach; (4) usefulness of the session content in terms of physical activity; and (5) satisfaction with interventionists. A separate exit survey is provided to the two groups and tailored to the respective exercise or stretching intervention completed.

### Intervention

2.7

#### Exercise group

2.7.1

Participants randomized to this group partake in a 16-week multicomponent exercise intervention consisting of a functional exercise warm-up and a resistance exercise circuit that is supervised in a clinic-based environment 3 days per week. The supervised sessions will be one-on-one, led by a certified exercise trainer in a hospital-based gym. Participants are also encouraged to complete self-directed home-based aerobic exercise on 4 days per week. Before beginning the supervised exercise, participants undergo a screening procedure to assess their bone pain level on a scale of 0–10. In the event bone pain is described, adjustments are made to the resistance exercise for that day to ensure the participant exercises in a pain-free motion.

Clinic-based component: Sessions begin with a dynamic warm-up of functional exercises that target aspects of balance, coordination, agility, and functional movements associated with tasks of everyday living (example exercises include calf raises, arm swings, and wrist rotations). The warm-up is followed by a circuit-based resistance program that is performed by alternating upper and lower body exercises in a single circuit. Participants complete four cycles (one cycle = 4 weeks) over the 16-week intervention. An orientation session (counting as their first session) takes place to introduce the study and exercises to the participant and to walk them through how a session will be run and what to expect in each cycle. The first session of each new cycle involves RM testing of each exercise to be prescribed in that 4-week cycle. During any session that is not considered a de-loading session, a 5%–10% increase in weight may occur when the participant can do >3 repetitions with good technique beyond what is prescribed and reports a low rate of perceived exertion (i.e., <7); this ensures participants are consistently working at the assigned RM. In each 4-week cycle, new exercises (Table 2) are introduced to provide variety and alternative stimuli to the body, while targeting the same muscle groups each session/cycle. While in Table 2, the primary exercises are described, alternative exercises that target the same muscle group may be used, subject to participant health and abilities. With this variety in exercises also comes variety in equipment, where machine weights, dumbbells, body weight, and resistance band exercises are incorporated throughout the 16-week intervention. The exercise intervention is periodized to ensure progressive overload and training adaptations. The prescription will be at an intensity ranging from 8 to 15 RM, completing 2–3 circuits of 6–15 repetitions of each exercise (Table 3). In addition, within each week, there will be two higher intensity days and one de-load day, again to provide variety and prevent overload. Each session will conclude with a cooldown incorporating stretches.

**Table 2 T2:** Example resistance exercises prescribed in each exercise cycle.

Exercise examples
Cycle 1: Machine-based Leg press, chest press, leg curl, seated row, leg extension, shoulder press
Cycle 2: Combination of machine and free weights Leg press, dumbbell bench press, dumbbell reverse lunges, seated row, dumbbell chair squat, dumbbell lateral raise
Cycle 3: Predominantly free weight-based Leg press, dumbbell bench press, resistance band deadlift, dumbbell bent over row, dumbbell chair squat, dumbbell shoulder press
Cycle 4: Combination of machine and free weights Leg press, chest press, glute bridge, alternating arm dumbbell row, dumbbell lunges, dumbbell shoulder press

**Table 3 T3:** Intervention periodization for the FIERCE 16-week intervention.

Weekly session number	Resistance training (supervised in-person)			Aerobic training (self-directed at home)	
	Weight intensity	Circuits	Reps	Intensity	Time
Cycle 1 (Week 1–4)					
1	15 RM	2–3^a^	15	60%–65% HRR	15 min/day
2	15 RM	2–3^a^	12		
3	15 RM	2–3^a^	15		
Cycle 2 (Week 5–8)					
1	12 RM	3	12	65%–70% HRR	20 min/day
2	12 RM	3	10		
3	12 RM	3	12		
Cycle 3 (Week 9–12)					
1	10 RM	3	10	70%–75% HRR	30 min/day
2	10 RM	3	8		
3	10 RM	3	10		
Cycle 4 (Week 13–16)					
1	8 RM	3	8	75%–80% HRR	30 min/day
2	8 RM	3	6		
3	8 RM	3	8		

HRR, heart rate reserve.

^a^
Two circuits are completed in the first week only.

Home-based component: Participants are offered an optional stationary bike to help complete self-directed aerobic exercise at home; however, participants may choose any form of aerobic exercise that suits their lifestyle. In addition, if they do not have one, participants are offered an activity monitor to monitor heart rate intensity. Aerobic exercise is completed on any day of the participant's choosing, 4 days per week, at an intensity of 60%–80% heart rate reserve for 15–30 min per day (Table 3). During the supervised sessions, exercise trainers record the reported home-based aerobic activity completed since the last supervised session and set goals with the participant for the upcoming week.

#### Control group

2.7.2

During this initial 16-week period, control participants are provided a booklet with the prescribed stretching program to be completed 7 days per week to match the prescribed frequency of exercise sessions in the exercise group, e.g., 3 days/week supervised circuit training plus 4 days/week self-directed aerobic exercise. The stretching program is self-directed home-based with instruction provided at baseline testing only to orient them with the booklet. Similar to the exercise program, the stretches change every 4 weeks, where 4–5 stretches that target both upper and lower body are prescribed. Participants in the attention control group are offered the supervised component of the 16-week intervention following the initial 16-week period.

### Intervention adherence

2.8

Exercise adherence is captured for the multicomponent exercise intervention by calculating (1) the percentage of supervised circuit trainings attended (out of 48 sessions) and self-directed exercise sessions completed (out of 64 sessions) and (2) relative dose intensities of supervised circuit trainings. Reasons for missed sessions will be documented throughout the study. However, to account for any unforeseen illness, family or medical emergency, or unplanned travel, all participants may have a total of 18 weeks to complete the 48 supervised exercise sessions. Participants are considered compliant if they attend ≥70% of the total prescribed number of supervised exercise sessions (e.g., attend ≥34 out of 48 sessions), ≥70% of the self-directed exercise sessions (e.g., complete ≥45 out of 64 sessions), and complete ≥70% of the supervised resistance sessions at the prescribed intensity. Participants are provided with monetary compensation for each optional muscle biopsy and testing visit and parking validation for every visit to Dana-Farber Cancer Institute.

### Adverse events

2.9

Any expected and unexpected adverse events are or will be reported to the principal investigator, who then subsequently reports to the institutional review board of the Dana-Farber Cancer Institute as per policy.

### Data monitoring and management

2.10

Data are monitored internally within the Dana-Farber Cancer Institute for timeliness of submission, completeness, and adherence to protocol requirements. Monitoring begins at the time of participant registration and will continue during protocol performance and completion. The study team collects, manages, and performs quality checks of the data. Potential audits or inspections may be conducted by the principal investigator or their designated representatives. All data are stored on a secure network drive using REDCap (Research Electronic Data Capture; Vanderbilt University), a Health Insurance Portability and Accountability Act-compliant web-based application hosted by Partners HealthCare Research Computing, Enterprise Research Infrastructure & Services, on password-protected computers. Any hard-copy data are stored in locked filing cabinets in card-access facilities. The results of this study will be presented in publication, conference, and invited speaker formats.

### Sample size calculation

2.11

We will enrol a total of 80 eligible participants. Considering a 10% attrition rate, the sample size of the analysis population will be 72. We plan to accrue participants for 24 months. The Wilcoxon rank-sum test will be used to compare the score based on the frailty phenotype (37) between the two groups for the primary analysis. Table 4 shows the anticipated distribution of the score in each group (59). With a sample size of 72, the study will have 84% to detect the relative effect of 0.30 at a 0.05 two-sided alpha level. This power calculation was performed by the WMWssp package (60). For comparing each of the five criteria of the frailty score (binary outcomes), the sample size of 72 will provide 80% power to detect a moderate effect size (Cohen's *h* = 0.415) at a 0.05 two-sided alpha level (61). For each continuous outcome, two-sample *t*-tests will be used for the between-group comparison as the primary analysis. Log transformation may be considered, if appropriate. With a sample size of 72, the study will have 80% power to detect a moderate to large effect size (Cohen's *d* = 0.67) at a 0.05 two-sided alpha level.

**Table 4 T4:** Sample size and power with the anticipated distribution of the frailty score (0–5).

Frailty status	Not frail (%)	Pre-frail (%)		Frail (%)			Total sample size	Relative effect	Power (%)
	0	1	2	3	4	5			
Attention control	15	63	17	4	1	0	72	0.30	84
Intervention	85	14	1	0	0	0			

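### Table 4's score distributions give a relative effect of 0.14 and power above 99.9%, not the stated 0.30 and 84%

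*Protocol article*

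**What the plan says.** Section 2.11 (Sample size calculation) names the test: "The Wilcoxon rank-sum test will be used to compare the score based on the frailty phenotype (37) between the two groups for the primary analysis". It then introduces the planning assumption: "Table 4 shows the anticipated distribution of the score in each group". The analysed number comes from 80 enrolled: "Considering a 10% attrition rate, the sample size of the analysis population will be 72". The conclusion is "With a sample size of 72, the study will have 84% to detect the relative effect of 0.30 at a 0.05 two-sided alpha level", and the section says that the WMWssp package was used.

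Table 4 is titled "Sample size and power with the anticipated distribution of the frailty score" and puts everything side by side. The first six numbers in each row are the percentages at scores 0 to 5. The control row ends with total sample size, relative effect and power:

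- "Attention control 15 63 17 4 1 0 72 0.30 84"
- "Intervention 85 14 1 0 0 0"

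Section 2.12 (Statistical analysis) confirms 1:1 allocation and the Wilcoxon rank-sum test as the primary analysis.

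**The concern.** For a rank-sum test on an ordered score, the relative effect is not a separate assumption. Once the two distributions are written down, it is fixed by them. A rise from 15% to 85% at score 0 is a very large separation of the arms and looks too large for a relative effect of 0.30.

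If the table disagrees with itself, the trial has two planned effects. One is a near-complete reversal, with 85% of the exercise arm at score 0. The other is a much smaller shift. This is the only power statement for the primary comparison, and a null or modest result would be read very differently against each.

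**Working it through.** **Inputs** (sections 2.11 and 2.12): control C = 0.15, 0.63, 0.17, 0.04, 0.01, 0; exercise T = 0.85, 0.14, 0.01, 0, 0, 0; N = 72, 36 per arm; two-sided alpha 0.05. Each row sums to 1, and 80 × 0.9 = 72 is correct.

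**1. The plan's own pair, 0.30 and 84%.** Noether's tie-free formula with equal arms is

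Power = Φ( √(N/4) × |p − 0.5| × √12 − 1.96 ).

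With p = 0.30 and N = 72: √18 × 0.20 × √12 = 2.939, and Φ(2.939 − 1.96) = Φ(0.979) = 0.836. So 0.30 and 84% are consistent with each other if ties are ignored.

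**2. Relative effect from the printed rows.** p = P(C < T) + ½ P(C = T).

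- P(C < T): exercise at 1 with control at 0, 0.14 × 0.15 = 0.0210; exercise at 2 with control at 0 or 1, 0.01 × 0.78 = 0.0078. Sum 0.0288.
- P(C = T): 0.85 × 0.15 + 0.14 × 0.63 + 0.01 × 0.17 = 0.1275 + 0.0882 + 0.0017 = 0.2174.
- p = 0.0288 + 0.1087 = **0.1375**. Reversing the groups gives 0.8625. Neither matches 0.30 or its mirror 0.70.

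**3. Power from the printed rows, allowing for ties.**

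Power = Φ( [√(N/4) × |p − 0.5| − 1.96 σ₀] / σ₁ ).

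- Null variance, from the pooled distribution 0.50, 0.385, 0.09, 0.02, 0.005: σ₀² = (1 − Σm³)/12 = 0.0681, σ₀ = 0.261.
- Alternative variance, the mean of the two arms' placement variances: (0.0347 + 0.0236)/2 = 0.0292, σ₁ = 0.171.
- At N = 72: √18 × 0.3625 = 1.538; 1.96 × 0.261 = 0.511; (1.538 − 0.511)/0.171 = 6.0. Power is above 99.9999%.

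A simulation of the tie-corrected Wilcoxon test at 36 per arm rejected in all of 20,000 trials.

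**4. Sample size the printed rows would need.** The same formula gives 83.5% at N = 14 and 89% at N = 16 (simulation at 8 per arm: 86.5%). Noether's formula gives about 23 for 84%.

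**5. Variants that might rescue the figures.**

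| Variant | Result |
|---|---|
| Scores collapsed to not frail / pre-frail / frail | p = 0.146, power above 99.99% |
| One-sided alpha | power above 99.99% |
| N = 80 | power above 99.99% |
| Noether's formula, p = 0.1375 | power 99.96% |

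None comes near 0.30 or 84%.

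**6. What 0.30 would look like (illustration only).** Two assumed exercise rows were compared with the printed control row:

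- A proportional-odds shift (common odds ratio about 5.2) gives about 48/47/4/1/0/0%, p = 0.30, and tie-adjusted power of about 93%.
- A mixture of 55% of the printed exercise row and 45% of the control row gives 53.5% at score 0, p = 0.301, and power of about 91%.

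Both put roughly half the exercise arm at score 0, not 85%.

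**The case against.** The strongest reply is that there is one mismatch here and not two, and that it has no consequence for the size of the trial. Relative effect 0.30 and power 84% agree with each other, and the text names 0.30 as the effect to be detected, so a result can be judged against 0.30 whatever the table shows. On the printed rows the trial is heavily overpowered. On 0.30 it has 84% power without ties and more under the illustrations above. The test, alpha, allocation and enrolment all stay.

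Much of this stands. The fault is a single break between the distributions and the relative effect, and it does not show an underpowered trial. It does not clear the plan, though: the text presents the table as the anticipated scenario, and the table's title ties the power to that scenario. Naming 0.30 does not settle which assumption the sponsor holds when the percentages beside it say 0.14.

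Two cautions about remedy also stand. The distribution is attributed to a cited source that is not available here, and either row could be the wrong one. Any replacement row solved backwards from 0.30 is therefore only an illustration. And the match with a tie-free formula is a possible explanation of the 84%, not an established one, since the article names the package but not the inputs.

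Other explanations fail. Table damage is unlikely because both rows have six cells and sum to 100%. A separate analysis plan could not help either, because nothing is missing: both sides of the contradiction are printed.

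**Conclusion.** The concern holds. As printed, Table 4 implies a relative effect of 0.1375 against the stated 0.30, and power above 99.99% against the stated 84%, at 36 per arm and two-sided alpha 0.05. For 84% power, 72 is about five times the number the printed scenario needs (72/14 ≈ 5.1).

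The relative effect rests only on the two printed rows. The power also rests on 1:1 allocation and on a large-sample formula, which simulation confirms. The statement that 0.30 would carry about 91% to 93% power with ties depends on assumed shapes for the exercise arm.

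This must be corrected because the stated basis for the primary comparison fails on its own inputs. It does not call the sample size of 80 into question.

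**What to change.** Go back to the inputs given to WMWssp and to the source of the distributions, re-run the calculation allowing for ties, and print one set of figures that agree in Table 4 and in the text of section 2.11.

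- **If 0.30 is the planned effect:** replace whichever row is wrong with the distribution actually assumed, check that it gives 0.30, and restate the power. The illustrative rows above should not be copied in as though they were sourced.
- **If the printed rows are the planned scenario:** restate the relative effect as 0.14 and the power as above 99.9%, and give the reason for enrolling 80, since those rows alone do not explain it.

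In either case, state the direction in which the relative effect is defined. The cost is one recalculation, one corrected table and one corrected sentence, with no extra patients and no change to the primary test.

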### Statistical analysis

2.12

This study will assess whether a 16-week, multicomponent exercise intervention will improve the frailty status of mPCa on ADT. Furthermore, we will assess the effect of the intervention on sarcopenia status, skeletal muscle-derived biomarkers, and cell proliferation rate.

A total of 80 eligible patients who complete the baseline assessment will be randomly assigned to the exercise or attention control groups in an allocation ratio of 1:1 using a permuted blocked design with varying block size (with investigators blinded to block size). The randomization will be stratified by frailty status (pre-frail vs. frail) at baseline assessment.

All analyses will be performed based on the intention-to-treat principle. We will repeat the same analyses with the subjects who complied with the protocol as secondary analyses. Baseline demographic and clinical measures, as well as baseline values of trial outcomes, will be presented by randomized intervention group; continuous measures will be summarized by mean (SD) or median (IQR) and categorical measures by frequencies (percent's). The randomized groups will be compared concerning baseline demographic and clinical variables using two-sample *t*-tests, Wilcoxon rank-sum tests, or Fisher's exact tests to confirm baseline comparability. These variables will be included in the adjusted analyses if clinically meaningful or statistically significant differences are identified.

The primary outcome is the score based on the Fried frailty phenotype (37), which consists of five criteria, and the score will take an integer value from 0 to 5. The Wilcoxon rank-sum test will be used as the primary analysis for comparing the score distribution between groups. Mean score and a corresponding 0.95 confidence interval (CI) will be calculated. We will also assess the intervention effect on each of the five criteria for the frailty phenotype for hypothesis generation purposes. For each, we will perform Fisher's exact test for the between-group comparison and estimate an odds ratio and a corresponding 0.95 CI. Regression analysis will be used to identify baseline factors associated with the outcomes, where proportional odds models will be used for the score as an ordered categorical variable with six categories, and logistic regression models will be used for each of the five criteria.

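### The 80% power stated for the five binary frailty criteria at Cohen's h = 0.415 does not follow from 72 participants: 36 per arm give about 42%, and less with the planned Fisher test

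*Protocol article*

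**What the plan says.** All the inputs are in two sections of the protocol article.

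- **Sample size calculation (2.11), numbers.** "We will enrol a total of 80 eligible participants". "Considering a 10% attrition rate, the sample size of the analysis population will be 72". Table 4 also lists 72 in its total sample size column.
- **Sample size calculation (2.11), binary criteria.** For each of the five components of the frailty score, "the sample size of 72 will provide 80% power to detect a moderate effect size (Cohen's *h* = 0.415"), with alpha 0.05 two-sided.
- **Sample size calculation (2.11), continuous outcomes.** For these, tested by two-sample t-test, "With a sample size of 72, the study will have 80% power to detect a moderate to large effect size", given as Cohen's d = 0.67, again at 0.05 two-sided.
- **Statistical analysis (2.12), allocation.** Participants are "randomly assigned to the exercise or attention control groups in an allocation ratio of 1:1".
- **Statistical analysis (2.12), test.** For each criterion "we will perform Fisher's exact test for the between-group comparison", with an odds ratio and its 0.95 confidence interval. The same section describes these five comparisons as serving hypothesis generation.

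**The concern.** Cohen's h is the difference between two arcsine-transformed proportions. Its large-sample power formula has the same form as that for a standardised mean difference. With the same total, alpha and power, the detectable h and the detectable d should therefore almost coincide. In this section they do not: d is 0.67 and h is 0.415.

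The Introduction's first hypothesis includes improvement in each individual frailty component, so readers will look at these five comparisons. If they rely on the stated 80%, they may take a non-significant component as fair evidence against a moderate effect. At the power the design has, a true effect of that size would be missed more often than found.

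**Working it through.** **Inputs.** 80 enrolled, less 10%: 80 × 0.9 = 72 analysed (2.11). 1:1 allocation (2.12): 72 / 2 = 36 per arm. Two-sided alpha 0.05, so z = 1.960; 80% power, so z = 0.842. Effect h = 0.415 (2.11).

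**1. The stated power.** By the arcsine normal approximation, power = Φ(h × √(n/2) − 1.960), with n per arm.

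- √(36/2) = √18 = 4.243
- 0.415 × 4.243 = 1.761
- 1.761 − 1.960 = −0.199
- Φ(−0.199) = 0.421

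The result is about 42%, against 80% stated.

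**2. The neighbouring figure, as a control.** The two-sample t-test with 36 per arm, d = 0.67 and two-sided 0.05 has 80.05% power (noncentral t). The continuous-outcome figure therefore reproduces, and it confirms that 72 is the total and not the size of each arm.

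**3. Detectable h at 80% power.** (1.960 + 0.842) / 4.243 = 0.66, next to d = 0.67 as expected.

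**4. Size needed for h = 0.415.** 2 × (1.960 + 0.842)² / 0.415² = 2 × 7.85 / 0.1722 = 91.1, so 92 per arm, or 184 analysed.

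**5. Other readings of the inputs (arcsine, h = 0.415).**

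| Reading | Power |
|---|---|
| 36 per arm, one-sided 0.05 | 54.6% |
| 40 per arm, two-sided | 45.9% |
| 72 per arm, two-sided | 70.2% |
| 80 per arm, two-sided | 74.7% |
| 72 per arm, one-sided 0.05 | 80.1% |
| One sample, n = 36, one-sided 0.05 | 80.1% |
| One sample, n = 72, two-sided | 94.1% |

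Only the two one-sided readings give 80%, and both conflict with the stated two-sided, two-group design with 72 in total.

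**6. The planned test.** Exact power of Fisher's test at 36 per arm, found by enumerating every pair of outcomes. The article gives no base rates for the criteria, so the proportions are assumed.

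| Proportions, h = 0.415 | Fisher power |
|---|---|
| 0.20 vs 0.064 | 27% |
| 0.30 vs 0.132 | 31.3% |
| 0.40 vs 0.211 | 32.5% |
| 0.50 vs 0.298 | 31.5% |
| 0.70 vs 0.498 | 31.4% |
| 0.90 vs 0.745 | 30.4% |
| 0.95 vs 0.824 | 24.2% |

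The maximum over all pairs with h = 0.415 is 32.6%.

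| Proportions, h = 0.66 | Fisher power |
|---|---|
| 0.20 vs 0.018 | 58% |
| 0.40 vs 0.121 | 71.4% |
| 0.50 vs 0.193 | 72.1% |
| 0.60 vs 0.279 | 70.9% |
| 0.70 vs 0.377 | 70.9% |

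So the corrected arcsine figure of 0.66 also does not carry 80% power once Fisher's test is used.

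**The case against.** The best defence concerns consequence, not arithmetic. The analysis section labels the five criteria hypothesis-generating. The planned size is supported by a separate Wilcoxon calculation for the composite score. Each criterion will be reported with an odds ratio and confidence interval, so imprecision will be visible whatever power was claimed. All of this stands, and it limits the seriousness of the error. It does not make the 80% true.

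Three stronger readings are tempting, and the document does not support them.

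- **That the trial is too small.** A reader might infer this from the 92 per arm. But the five criteria do not determine the sample size, and this error does not touch the primary calculation.
- **That the authors used 72 per arm with a one-sided test.** This does give h = 0.414 at 80% power, but a one-sample, one-sided calculation with n = 36 fits identically. The article states neither, so any account of how 0.415 arose is inference.
- **That the d = 0.67 statement is also wrong, because** "Skeletal muscle biopsies of the vastus lateralis are optional". That statement is explicitly conditional on 72 participants and is correct on that condition. No biopsy uptake is given, and a separate figure for an optional subset is detail that an article may leave to the full protocol.

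**Conclusion.** The stated power is wrong as written. At h = 0.415 with 36 per arm and two-sided 0.05 it is about 42% by the arcsine approximation, roughly half the claimed 80%. That result uses only figures in the article. The Fisher figure of roughly 30–33% depends on assumed mid-range proportions and falls towards the extremes. These are chances of detecting an effect of exactly h = 0.415; larger effects would fare better.

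Severity is moderate: this should be corrected, but it is a supporting figure for non-confirmatory comparisons and leaves the primary analysis and the planned size untouched.

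**What to change.** Replace the binary-criteria sentence in the sample size section in one of two ways:

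- State that 36 per arm give 80% power at two-sided 0.05 for h of about 0.66. Label this an arcsine approximation, and add that Fisher's exact test has about 70–72% power at that effect for mid-range proportions and less near 0 or 1.
- Or state, for explicit assumed control proportions, the intervention proportions detectable with 80% power under Fisher's test.

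Swapping 0.415 for 0.66 while keeping an unqualified 80% would not be enough, because the planned test does not reach it. The wording should also stop calling the detectable effect moderate, since it matches the d = 0.67 that the next statement calls moderate to large.

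The cost is one rewritten sentence and a less favourable figure. Sample size, tests and trial conduct do not change.
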